#### 2.6.3. Physical Activity and Sleep Behavior

A Fitbit accelerometer will be provided to all participants. Participants will be asked to wear the Fitbit on their wrist for seven days after the baseline data collection visit and seven days prior to the post-intervention data collection visit. The data will be processed using Fitabase (Small Steps Labs, LLC, San Diego, CA, USA) software (https://www.fitabase.com/, accessed on 22 January 2024). The purpose of accelerometry data is to determine changes in physical activity and sleep behaviors at baseline and after completing the 8-week intervention. Participants will not have to return the Fitbit throughout or after the study.

#### 2.6.4. Circulating Biomarkers 

Fasting (12 h) venous blood samples will be obtained and processed for plasma and serum; the blood will be stored at −80 °C or shipped for analysis. Glycated hemoglobin from whole blood, serum glucose, and serum insulin will be analyzed by a local commercial lab (Quest Diagnostics, Wood Dale, IL, USA). Insulin resistance will be calculated using the following homeostasis model assessment (HOMA) method: (HOMA-IR = fasting insulin [microinsulin units/milliliter] × fasting glucose [milligrams/deciliter]/405). Serum tryptophan and tryptophan metabolites (i.e., kynurenine, kynurenic acid, serotonin, and quinolinic acid) will be measured by mass spectrometry at the University of Illinois Chicago Metabolomics and Proteomics Core (Chicago, IL, USA). All samples will be measured in duplicate by a lab technician blinded to randomization assignments.

#### 2.6.5. Blood Pressure, Heart Rate, and Heart Rate Variability

Blood pressure will be assessed in duplicate with the participant in a seated position after a 10-min rest and a 5-min rest between measurements (Omron, Kyoto, Japan). Heart rate and heart rate variability will be measured for 7 days (24-h analysis) via Fitbit after the baseline data collection visit and 7 days prior to the post-intervention data collection visit. 

#### 2.6.6. Stool Collection

During the baseline visit, participants will be instructed regarding home stool collection and will receive two stool collection kits (one for baseline assessment and one for post-intervention assessment). Stools will be collected at home after the baseline visit using the kit provided by the study team. The stool kit will have a pre-labeled envelope. After collecting the sample, participants will mail the sample to the research team using a pre-labeled envelope that will be delivered within two days of shipment. The research team will provide the OMNIgene-GUT tube (DNA Genotek, Ottawa, ON, Canada) to the participants. This tube collects and stabilizes DNA for quantitative gut microbiome profile analysis and is stable at room temperature for 60 days post-collection. A Bristol stool scale will also be completed by the participant [46]. Upon receipt, stool will be aliquoted, and a portion will be processed for the calprotectin assay and stored at −80 °C until analysis. 

#### 2.6.7. Microbial Amplicon Sequencing and Bioinformatics Processing

16S rRNA amplicon sequencing will be performed using microbial DNA extracted from participant stool samples. Sample preparation and analysis will be conducted by the University of Illinois Genomics Core. The V4 region of the 16S rRNA gene will be amplified and sequenced with the Illumina MiniSeq platform (Azenta Life Sciences, Burlington, VT, USA). Environmental controls will be included in the sequences to distinguish any contaminants. Moreover, 16S rRNA reads will be processed with DADA2 (version 3.11) [47] to identify the number of counts of amplicon sequence variants (ASVs). ASVs with a low number of counts or with a low abundance (<1%) will be removed from downstream analysis. ASVs will be summarized at different phylogenetic levels and normalized using cumulative sum scaling [48]. Variation in community structure alpha (i.e., Shannon) [49] and beta diversity (e.g., Bray-Curtis distances) [50] in response to the intervention will be determined within and between groups with the vegan [51] and phyloseq [52] packages in R (R Foundation for Statistical Computing, Vienna, Austria). Compositional differences will be determined using zero-inflated generalized liner mixed models correcting for covariates (e.g., BMI, sex, age) using MaAsLin2 (version 3.18) [48,53].

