#### 2.6.12. Power and Sample Size 

This study is designed to evaluate the feasibility of the development of a larger study. The goal of the trial is to investigate and learn about data management, data collection methodologies, and how to design a larger study in the future. Forty-eight adults will be recruited, allowing for a 20% dropout rate, resulting in completed data collection on 40 individuals, which supports the calculation of confidence intervals for feasibility and effect size components. This feasibility-pilot study is not powered to detect statistically significant effects for improvement in chronic stress and body weight or the secondary/exploratory measures. The minimum detectable difference for these outcomes is 1 standard deviation based on the sample size in each of the four groups (n = 10/arm) between the baseline and post-intervention measurements that are correlated at r = 0.5, alpha = 0.05, and 80% power. We expect that there will be no change between baseline and post-intervention measurements in the control group. We did not consider power for the overall and multiple pairwise comparisons between different groups, nor will we correct for multiple comparisons because of the exploratory nature of the pilot study [67,68,69,70,71]. 

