Exploratory inferential statistics will be conducted, but no conclusions on the efficacy of the interventions will be drawn from the results. Initially, we will evaluate distributions, identify any outliers, and look for patterns of missing data. The continuous endpoints (stress, body weight, body composition, and cardiometabolic health) will be estimated among each of the groups, and the 95% confidence interval will be constructed assuming normal distribution, respectively. Then, a two-sample *t*-test will be utilized to compare each of the three intervention groups and the control group. GLM will be employed to estimate the adjusted difference in each of the continuous endpoints between the different groups. We will also investigate co-primary (body, weight, objective stress markers) and secondary outcomes (i.e., body composition, PSS, cardiometabolic measures) for between- and within-treatment differences and test for (treatment) × (time) interactions to compare the trends over time using generalized linear mixed models. We will investigate changes in microbial community diversity and composition (ASVs), tryptophan-related metabolites, and systemic and intestinal inflammation changes from baseline to post-intervention by treatment arm. The other binary endpoints will be compared between the different groups using Fisher’s exact test or chi-square test, respectively. Multivariate logistic regression will be further employed to compare these binary endpoints between the different groups, after adjusting for plausible confounders. Odds ratios and 95% confidence intervals will be calculated to evaluate the strength of any association that emerges.

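### The 1% abundance filter on ASVs is applied, as written, before Shannon and Bray-Curtis; its basis is undefined and it can hide an effect confined to rarer taxa

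*Protocol article*

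**What the plan says.** Section 2.6.7 sets out the sequencing pipeline in order. After read processing, "ASVs with a low number of counts or with a low abundance (<1%) will be removed from downstream analysis". Next, "ASVs will be summarized at different phylogenetic levels and normalized using cumulative sum scaling". The two diversity indices follow: Shannon for alpha diversity and Bray-Curtis for beta diversity, within and between groups. Last come the taxon models: "Compositional differences will be determined using zero-inflated generalized liner mixed models correcting for covariates (e.g., BMI, sex, age) using MaAsLin2". The section makes no exception for diversity. It does not define the count cut-off or what the 1% refers to, and it names no false discovery rate or q threshold.

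Section 2.7 plans to examine change in microbial diversity and composition by arm. The Introduction lists the gut microbiome among the secondary outcomes.

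On multiplicity, Section 2.6.12 ends a sentence about power for comparisons between groups with "nor will we correct for multiple comparisons because of the exploratory nature of the pilot study". Taxon-level tests are not mentioned there.

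**The concern.** Shannon diversity depends on the number of variants present and on how evenly reads are spread over them, so the many low-abundance variants contribute a good part of it. For a single sequence variant, 1% is a high bar. If variants below it are removed first, the index describes only the dominant part of the community. An intervention that acts on rarer taxa could then show little or nothing in the diversity endpoint. An abundance filter is normally justified by the taxon-by-taxon models, where sparse variants give unstable fits; diversity does not need it.

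The undefined basis adds to this. Three reasonable readings of the 1% give three different endpoints, and the choice could be made after the data are seen.

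The second issue is smaller. The taxon models produce many tests, and the only statement on multiplicity in the article declines correction without exempting them. Section 3 says the preliminary data will help develop a fully powered trial, so an attenuated diversity effect or an unscreened list of taxa could mislead that work.

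**Working it through.** **The plan's own figure.** The article gives no figure for the microbiome analysis. Its only power figure is a minimum detectable difference of 1 SD with 10 completers per arm and "measurements that are correlated at r = 0.5, alpha = 0.05, and 80% power". With r = 0.5 the SD of change is SD × √(2(1 − 0.5)) = SD. A paired t-test (two-sided, assumed) with n = 10 has power 0.803 at 1 SD, and 80% power at 0.996 SD, so the figure reproduces. It is a within-arm figure: comparing change between two arms of 10, a 1 SD difference has power 0.56 and the detectable difference is 1.32 SD. There is little precision to spare for an endpoint whose effect has been attenuated.

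**Effect of the filter on the indices.** Assumptions: 96 samples (48 participants × 2 visits), log-normal communities of 150 or 300 ASVs, 20,000 reads per sample, and the 1% read three ways. Aggregation and cumulative sum scaling were not simulated.

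| Reading of 1% | ASVs left per sample | Reads kept | Fall in mean Shannon | Change in mean Bray-Curtis |
|---|---|---|---|---|
| Study mean | 20 to 31 | 52% to 75% | 0.8 to 1.7 (e.g. 4.05 to 2.62; 3.99 to 2.32) | down 0.02 to 0.03 |
| Per sample | 16 to 24 | 64% to 84% | 0.7 to 1.4 (e.g. 4.05 to 2.81) | up 0.07 to 0.18 (e.g. 0.47 to 0.65) |
| Maximum in any sample | 90 to 157 | 94% to 98% | 0.1 to 0.2 | at most 0.01 |

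A second simulation (100 to 250 ASVs, log-scale SD 1.5 to 2, 30,000 reads) agrees: 18 to 24 ASVs survive a 1% cut, 16% to 45% of reads are lost, and Shannon drops from 3.0–4.4 to 2.3–2.9.

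**Effect on an arm comparison.** A lower level does not by itself bias a comparison, so the arm difference was simulated directly: two arms of 10, pre and post, 150 or 300 ASVs, with the rarer ASVs (mean abundance below 0.4%) doubled in one arm. The between-arm difference in Shannon change was:

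- unfiltered: 0.18 to 0.32
- study-mean rule: about 0 (−0.02 to 0)
- per-sample rule: 0.08 to 0.11, about a third of the unfiltered value
- maximum rule: 0.12 to 0.19, a loss of about a third or more (e.g. 1 − 0.13/0.20 = 35%)

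**Taxon tests.** If every taxon is null, expected false positives = taxa × contrasts × alpha. Alpha is taken as 0.05, an assumption, since the article gives 0.05 only for the detectable difference. With about 20 surviving taxa and three arm-versus-control contrasts, 20 × 3 × 0.05 = 3. If the tests were independent, the chance of at least one would be 1 − 0.95^60 = 0.95.

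**Share of nominal findings that are false.** With π the share of taxa that truly change, this is (1 − π) × 0.05 / [(1 − π) × 0.05 + π × power].

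- π = 10%, power 20%: 0.045 / (0.045 + 0.020) = 69%
- π = 30%, power 20%: 0.035 / (0.035 + 0.060) = 37%
- π = 20%, power 80%: 0.040 / (0.040 + 0.160) = 20%
- π = 0: 100%

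The article gives neither π nor power for these tests.

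**The case against.** **The filter is common to all arms and visits.** Filtered and unfiltered Shannon correlate at 0.84 to 0.94 under a study-mean rule, which might seem to protect the comparison. That correlation comes from communities with no effect on rare taxa. When there is such an effect, the simulation above shows that it can disappear. What stands is that this is a constructed scenario: nothing in the article says that the interventions act mainly on rare taxa, and an effect on dominant taxa need not be lost in this way.

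**The result depends on an undefined rule.** This stands. Under a maximum rule the level of both indices hardly moves, and under a study-mean rule Bray-Curtis hardly moves. The simulations also omit aggregation and scaling, although neither step can restore reads already removed.

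**The multiplicity sentence is about arms.** It sits in the power section and follows a clause on pairwise group comparisons. A journal article may also leave a q threshold to the analysis plan, and whether the software adjusts by default cannot be checked here. This reduces the second issue to a secondary one. The sentence is nonetheless general and names no exception; if adjusted values are intended, Sections 2.6.7 and 2.6.12 need reconciling.

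**Stronger readings.** A reader might infer that most taxon findings will be noise. The documents do not support that, because the false share runs from 20% or less to 100% depending on quantities they do not give. A strict filter also reduces the number of tests, although testing at several phylogenetic levels adds some back. A reader might also infer that diversity effects will be reversed. A case can be built in which 50 taxa added at 0.2% each raise true Shannon by 0.35 while filtered Shannon falls by 0.08, but nothing in the article points to such a shift.

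**The analyses are exploratory.** Section 2.7 rules out efficacy conclusions, and the primary outcomes are feasibility and acceptability. This limits the harm.

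**Conclusion.** The concern holds for the order of steps. As written, the filter precedes Shannon and Bray-Curtis, and the basis of the 1% is not fixed. Under assumed log-normal communities, a study-mean or per-sample rule leaves about 20 ASVs and lowers Shannon by roughly 0.7 to 1.7. All three readings attenuate a Shannon effect confined to rarer taxa, from about a third lost (maximum rule) to nearly all lost (study-mean rule). The effect on Bray-Curtis is material mainly under a per-sample rule. These sizes rest on the assumed communities and the assumed rare-taxon effect, so they show what the filter can do and do not forecast this trial's data.

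The multiplicity issue is secondary: about 3 false positives for 20 null taxa and 3 contrasts at an assumed 0.05. No claim is made about what share of taxon findings would be false. Overall severity is minor to moderate.

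**What to change.** 1. Compute Shannon and Bray-Curtis on the ASV table after contaminant removal and depth normalisation, with no abundance filter.
2. Confine the abundance or prevalence filter to the MaAsLin2 taxon models. Define it before the data are seen: the count cut-off, the abundance threshold and its basis, and whether it is applied before or after aggregation to higher taxonomic levels.
3. In Section 2.6.12, exempt the taxon tests from the statement on multiple comparisons and report Benjamini-Hochberg q-values per contrast, alongside the unadjusted p-values if wanted.

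No new data, visits or participants are needed: two pipeline steps are re-ordered and one column is added to the output. The downside is that fewer taxa will be called changed.

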#### 2.6.8. Colonic Inflammation

Fecal calprotectin is a non-invasive marker of intestinal inflammation [54]. From stool at baseline and post-intervention, fecal calprotectin will be assayed using a commercially available immunoassay kit (Bühlmann Diagnostics, Amherst, NH, USA). The lower level of detection for this assay is 32.5 μg/g. Values below the lower limit of detection are assigned a value of 16.25 μg/g per assay instructions. Values above 100 μg/g are suggestive of intestinal inflammation.

#### 2.6.9. Hair Cortisol (HCORT)

Participants will be able to decide if they are willing and able to provide hair samples (i.e., it is an opt-in measure). We will assess hair cortisol (HCORT) from a 2 cm scalp hair sample (one month’s growth represents cortisol deposition over the previous month) [55,56]. HCORT is a robust marker of the recent past (i.e., weeks or months) or an ongoing stressor that is responsive to Mindfulness [57]. Hair will be taken by the research team during the data collection appointment from the crown and vortex of the head and stored at −80 °C until analysis. Hair health will also be considered when collecting hair samples. Each hair sample will be weighed, washed twice with isopropanol, and air-dried for a minimum of 24 h. Methanol will be added to the powdered hair, and the cortisol will be extracted. Tubes are centrifuged, after which methanol extract is removed to a clean tube and evaporated using a vacuum evaporator. The dried extract is reconstituted in an assay buffer, filtered to remove particulate material, and then frozen for subsequent assays. The cortisol content of the extract is analyzed in duplicate with the control via immunoassay (Enzo Lifesciences, Farmingdale, NY, USA), which is converted to pg cortisol/mg dry hair weight, as the ELISA-based measurement of HCORT is more sensitive compared to mass spec [58]. Baseline and post-intervention samples for a participant will be assayed on the same plate.

#### 2.6.10. Adverse Event Monitoring

Intervention-related adverse events will be monitored via a standardized questionnaire and documented weekly through REDCap during the weekly check-in call. The questionnaire includes questions about gastrointestinal symptoms (nausea, vomiting, constipation, diarrhea), nervous system symptoms (dizziness, weakness, headache, fatigue, irritability, and unhappiness), any additional medication taken, COVID vaccine administration, and COVID positive status in the past week. Events will be classified according to a standardized coding scheme [59].

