### 2.1. Study Design 

This study is an 8-week, parallel-arm, randomized controlled trial (Figure 1). A total of 48 young adults (18–39 years old) with obesity [body mass index (BMI) between 30–49.9 kg/m^2^] and a Perceived Stress Score ≥ 14 [43] will be randomized 1:1:1:1 to the following groups: 1. TRE; 2. Mindfulness; 3. TRE and Mindfulness; or 4. Control.

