#### 2.4.1. Time-Restricted Eating (TRE)

Participants will be instructed to eat ad libitum from 12:00–8:00 p.m. daily and fast during the remaining hours (16-h fast). The set eating window was selected based on an observational study of 800,000 North Americans, which found that individuals usually place their TRE eating window from 12–8 p.m. so that they can have lunch and still eat dinner with friends and family [44]. During the 8-h eating window, there will be no restrictions on the types or quantities of foods consumed. In addition, participants will not be required to monitor calorie intake. During the fasting period, participants will be encouraged to drink plenty of water and consume energy-free beverages only, such as black tea or coffee. Participants will meet with a registered dietitian for 30 min at the start of the intervention to review instructions and goals and weekly thereafter. Weeks 2–8 will focus on TRE adherence and personalized problem solving related to adherence to the TRE intervention. Each day, participants will respond to a text message to indicate their eating start and stop times. If the message indicates that the participant ate only within the prescribed eating window (±30 min of 12 p.m. and + 30 min of 8 p.m.), that day will be labeled “adherent”, otherwise the day will be labeled “non-adherent.” On the same day and time each week, participants will be asked to transmit a picture of their weight from a home scale via a secure text-messaging platform. Participants will be asked to maintain their baseline level of physical activity.

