#### 2.4.4. Control

The control group will not receive any of the interventions described. To maintain a relationship with each participant in the control group, we will contact them once a week via phone. Participants will be asked to maintain their baseline level of physical activity. At the end of the intervention period, and after all data is collected, the registered dietitian will meet with the participants for 30 min and educate them regarding the TRE protocol and provide access to the Calm.com platform. 

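### The adverse event section limits monitoring to intervention-related events, a label that cannot apply to the control arm and conflicts with its own cause-neutral questionnaire

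*Protocol article*

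**What the plan says.** The scope of harm monitoring is set in section 2.6.10 of the protocol article: "Intervention-related adverse events will be monitored via a standardized questionnaire and documented weekly through REDCap during the weekly check-in call". The same section describes the form: "The questionnaire includes questions about gastrointestinal symptoms (nausea, vomiting, constipation, diarrhea), nervous system symptoms" (dizziness, weakness, headache, fatigue, irritability and unhappiness), and then "any additional medication taken, COVID vaccine administration, and COVID positive status in the past week". The only later step is "Events will be classified according to a standardized coding scheme". The article gives no rule for judging relatedness and names no one to judge it.

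All arms have weekly contact:
- TRE (2.4.1): "Participants will meet with a registered dietitian for 30 min at the start of the intervention to review instructions and goals and weekly thereafter".
- Mindfulness (2.4.2): a weekly staff contact about engagement and questions.
- Control (2.4.4): "The control group will not receive any of the interventions described", but "To maintain a relationship with each participant in the control group, we will contact them once a week via phone".

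Participants are selected for stress (2.1): "Perceived Stress Score ≥ 14".

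**The concern.** The ten listed symptoms are non-specific, and several are plausible in people enrolled for high perceived stress, whatever their arm. For one participant it is hard to say whether a headache or a bad week came from fasting. The sound basis is the rate in a concurrent untreated group, and this trial has one that is already phoned every week.

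A scope limited to intervention-related events puts that at risk, because an arm with no intervention cannot have an event related to one. The section can therefore yield two different datasets: every reported symptom in four arms, or only attributed symptoms in three. Staff building the form or the listing could follow either. Since the trial is meant to inform a larger study, the tolerability data are part of its product, and symptom reports not recorded at the time cannot be reliably recovered later.

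**Working it through.** The article states no adverse event figure, so there is none to reproduce. The check is mainly a comparison of its sections.

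**Step 1: label against control arm.** Section 2.6.10 monitors intervention-related events. Section 2.4.4 gives controls no intervention. Taken literally, no control event can qualify.

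**Step 2: label against questionnaire.** The form asks about ten symptoms without asking the cause. It also collects medication use, COVID vaccination and COVID status, which are not effects of TRE or Mindfulness. A form with these items collects more than its stated scope allows, so label and form conflict within one section.

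**Step 3: is a filter described?** No. The section does not restrict the questionnaire by arm, and controls have a weekly call at which it could be given. The article does not say outright that they are asked the same questions.

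**Step 4: is a between-arm harm comparison described?** Not by name. Adverse events are not among the primary or secondary outcomes in the Introduction, nor are they named in section 2.7. That section sends other binary endpoints to Fisher's exact or chi-square tests, which could take in adverse events but does not say so.

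**Step 5: is there a pre-intervention reading?** Section 2.6 opens with a default of baseline and post-intervention, unless stated otherwise; 2.6.10 states weekly calls instead. Health history, stress, anxiety, depression and sleep measures (2.6.11) and the Bristol stool scale (2.6.6) give partial baseline context for mood, sleep and stool. No baseline measure of nausea, vomiting, dizziness, weakness or headache is described.

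**Step 6: what a filter could remove (illustration).** The weekly probability *p* that a control reports any listed symptom is an assumption; the documents give none. With 8 weekly calls treated as independent and 48/4 = 12 controls all followed, the share with at least one report is 1 − (1 − *p*)^8:

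| Assumed *p* | 1 − (1 − *p*)^8 | Expected of 12 |
|---|---|---|
| 0.02 | 1 − 0.98^8 = 15% | 1.8 |
| 0.05 | 1 − 0.95^8 = 34% | 4.0 |
| 0.10 | 1 − 0.90^8 = 57% | 6.8 |
| 0.20 | 1 − 0.80^8 = 83% | 10.0 |

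If every report is kept, a control count of zero is unlikely except at the lowest rate: its probability is (1 − *p*)^96, which is 14% at *p* = 0.02 and 0.7% at *p* = 0.05. If only attributed events are kept, the control count could be zero at any of these rates. Symptoms that recur in the same people would lower the shares in the table.

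**The case against.** The strongest reply is that one loose adjective is being read as a procedure. The form is standardized and cause-neutral, nothing excludes controls from it, and this is a low-risk 48-person pilot. A condensed article may also leave the definition of relatedness, and any baseline use of the form, to the full protocol.

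Much of this stands, and it rules out several stronger readings that a reader might infer:
- *The control arm has no events by definition.* This follows only if the label is applied as a filter, and no filter is described.
- *Staff who know the assignment decide relatedness.* The article gives nobody that role; the dietitian's weekly meeting carries no causality task.
- *The harm comparison is biased.* No such comparison is specified. Bias would arise only if attributed counts were compared between arms.
- *The missing baseline reading biases the comparison.* Randomization balances pre-existing symptoms in expectation. What is lost is within-person judgement and some precision.
- *The days after the last call go uncovered.* The final call is not dated relative to the post-intervention visit, so no gap can be shown.

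The reply does not remove the conflict. The article is not silent on scope. It states one, and that scope disagrees with the control arm's description and with the form beside it. A fuller document might resolve this, but the published text points the wrong way.

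**Conclusion.** The point holds as a stated scope that conflicts with the design, and it should be corrected. It is a conditional risk, not a demonstrated bias: the control arm loses its use as a background rate only if the label is applied as a filter, and distortion follows only if attributed counts are then compared. The documents support no estimate of size. The figure of roughly 2 to 10 of 12 controls rests wholly on assumed weekly rates of 2% to 20%, independent weeks and full follow-up. The absent baseline reading is a secondary weakness, confined to telling new or worsened symptoms from existing ones. The low cost of the change, more than any proven harm, makes it worth doing in a pilot.

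**What to change.** Reword the opening of section 2.6.10 along these lines: *All adverse events and symptoms, whatever their presumed cause, will be recorded in all four arms with the same questionnaire, at the baseline visit before randomization and at each weekly call. Relatedness is held in a separate field and does not decide whether an event is recorded. Events will be reported by arm regardless of relatedness.* Section 2.4.4 should say that the control call includes the questionnaire.

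The baseline use fits the existing schedule, since section 2.3.4 places randomization after baseline data collection. The cost is one wording change, one relatedness field in REDCap and one short form added to an existing visit. The downside is a longer event listing with more unrelated entries. Treatment, sample size and visit schedule do not change.
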